## Abstract

**Background:**

About 30-60% of individuals are non-adherent to their prescribed medications and this risk increases as the number of prescribed medications increases. This paper outlines the development of a consumer-centred *Me*dicine *S*elf-*M*anagement *I*ntervention (MESMI), designed to improve blood pressure control and medication adherence in consumers with diabetes and chronic kidney disease recruited from specialist outpatients' clinics.

**Methods:**

We developed a multifactorial intervention consisting of Self Blood Pressure Monitoring (SBPM), medication review, a twenty-minute interactive Digital Versatile Disc (DVD), and follow-up support telephone calls to help consumers improve their blood pressure control and take their medications as prescribed. The intervention is novel in that it has been developed from analysis of consumer and health professional views, and includes consumer video exemplars in the DVD. The primary outcome measure was a drop of 3-6 mmHg systolic blood pressure at three months after completion of the intervention. Secondary outcome measures included: assessment of medication adherence, medication self-efficacy and general wellbeing. Consumers' adherence to their prescribed medications was measured by manual pill count, self-report of medication adherence, and surrogate biochemical markers of disease control.

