### Study aims

The primary aim of the study were to evaluate the effectiveness of a multifactorial intervention in terms of improved systolic blood pressure control in participants with co-existing diabetes and chronic kidney disease. Secondary aims were to determine the effectiveness of the intervention on medication adherence, medication self-efficacy and general wellbeing in consumers with co-existing diabetes and chronic kidney disease. The extent of the relationship between pill counts, self-report of medication adherence and self-efficacy, and other clinical and surrogate biochemical markers of disease control will also be evaluated.

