### Study hypotheses

1. Compared to participants receiving standard care, participants with diabetes and chronic kidney disease who receive the intervention will show greater reduction in blood pressure at three months post-intervention (T3).

2. Compared to participants receiving standard care, participants with diabetes and chronic kidney disease who receive the intervention will show a greater adherence to their prescribed medication regimen at three months post-intervention (T3).

3. Improved medication adherence will be associated with increased systolic blood pressure control at three months post-intervention (T3).

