### Medication review

The individualised medication review involved the intervention nurse drawing up a chart of the participant's prescribed medications as documented by the research assistant at the enrolment visit (T1), which included the generic and brand name of the medication, what the medication was for, the dose and when to take it, and targets for which to aim. Targets included a blood pressure ≤130 mmHg, blood glucose of < 7 mmol/L, Hb A_1C _< 7%, and low density lipoprotein (LDL) cholesterol < 2.5 mmol/L as recommended by Harris [18]. Prescription reconciliation, the process of comparing the participant's reported medication regimen to all of the medications that the participant has been taking, was conducted. Any areas of ambiguity with what participants thought they should be taking compared with what was prescribed according to pill containers and medication lists were sorted prior to obtaining agreement of the prescription. For example, one participant was taking duplicate cholesterol-lowering drugs that were the same but had different brand names. The medication chart was left with the participants as their personal medication record to take to medical consultations if they did not have a current medication list, and to note changes in their prescriptions as they occurred.

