### Feasibility of study

In the planning stages of the study in 2006, we found that more than 1,400 patients with diabetes at the hospital where recruitment was to take place had urine microalbumin/creatinine ratios ranging from 2 to an extreme of 6020 mg/mmol, with an average microalbumin/creatinine ratio of 97 mg/mmol suitable for our recruitment purposes. Additionally, the renal department at the hospital is one of the largest renal services in Australia treating in excess of 2,300 patients annually with chronic kidney disease. The base rate of systolic blood pressure control > 130 mmHg in the nephrology outpatient clinic population was estimated to be about 50%.

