### Patient eligibility

The inclusion criteria for the MESMI study are listed in Table 1. The primary outcome was systolic blood pressure control, taken by the research assistant who was trained to take blood pressure according to accepted guidelines [17] using an Accosson mercury desk sphygmomanometer and 3M™ Littmann classic 11 S.E. stethoscope. Participants were to avoid smoking, exercise and caffeine for 30 minutes while they were waiting for their clinic consultation and were seated for approximately five minutes prior to having their blood pressure measured.

**Table 1 T1:** Inclusion and exclusion criteria for the MESMI study

Inclusion criteria	
*****	Patients of either gender aged ≥ 18 years of age
*****	Able to comprehend English (English proficiency test > Not at all)
*****	Mentally competent (Abbreviated Mental Test score > 6)
*****	Type 1 or Type 2 diabetes recorded in patient's medical record
*****	Chronic kidney disease defined by an estimated Modified Diet in
*****	Renal Disease glomerular filtration rate (MDRD-eGFR) of ≤ 60 mL/min/1.73 m^2 ^and/or:
*****	Diabetic kidney disease defined by Malb/Cr ratios > 2.0 mg/mmol for men, > 3.5 mg/mmol for women or an elevated 24 hour urine albumin of > 30 mg over 24 hours
*****	Systolic hypertension ≥130 mmHg for the previous two clinic visits & prescribed antihypertensive medication/s
	

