### Power analysis

We based our sample size on Gerin et al.'s [35] medication adherence and blood pressure control (ABC) research, using the standard deviation for systolic blood pressure of 12.1 mmHg cited in the usual care systolic blood pressure group. The sample size determined to allow the detection of a mean (± SD) difference in systolic blood pressure of 3-6 mmHg between the intervention and control groups. The sample size calculation has yielded 51 participants per group with 80% power (a = 0.05 [one-tailed], including 5% attrition, totalling 108 participants in all.

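### The primary outcome is worded inconsistently: a planning effect and an undefined term stand in for the between-group difference in mean systolic pressure on which the trial is sized

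*Protocol article*

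**What the plan says.** The Protocol article describes the primary outcome in several places.

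- **Abstract, Methods:** "The primary outcome measure was a drop of 3-6 mmHg systolic blood pressure at three months after completion of the intervention". No comparison group is named.
- **Study aims:** the primary aim is "improved systolic blood pressure control in participants with co-existing diabetes and chronic kidney disease".
- **Patient eligibility:** "The primary outcome was systolic blood pressure control, taken by the research assistant". The sentence goes on to name the sphygmomanometer and stethoscope. No cut-off is given.
- **Study hypotheses:** hypothesis 1 is that intervention participants, compared with standard care, "will show greater reduction in blood pressure at three months post-intervention (T3"). It does not say systolic, or whether a T3 level or a change from baseline is meant.
- **Power analysis:** the trial is sized on a mean "difference in systolic blood pressure of 3-6 mmHg between the intervention and control groups", with SD 12.1 mmHg, one-tailed alpha 0.05, 80% power and 5% attrition, giving 51 per group and 108 in total.
- **Data analysis:** blood pressure is compared between groups and within participants at T2, T3 and T4 by t-tests. No adjustment for baseline is named.

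The figure 130 mmHg appears in other roles: an entry criterion (Table 1), a participant goal in Medication review ("Targets included a blood pressure ≤130 mmHg"), and a feasibility estimate ("The base rate of systolic blood pressure control > 130 mmHg", put at about 50%).

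**The concern.** A primary outcome should tell the reader what is measured, when, and how the groups are compared. The Abstract gives the size of effect hoped for instead. Taken literally, it would count a 10 mmHg fall as outside the outcome, and it does not say whose drop is compared with whose. The term control suggests a yes/no status, and the Feasibility section does use it with a threshold and a percentage, yet no outcome threshold is set. Hypothesis 1 is comparative but leaves the measure open.

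Two things are at stake. The stated power belongs to one form of the endpoint only, so a reader cannot tell from the outcome statement whether the 80% applies. And writing the planning effect as a range hides the single value that produced the sample size. The range also looks like a criterion for success, which the trial is not sized to meet at its lower end.

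**Working it through.** **1. Reproduce the stated sample size.** Inputs from the Power analysis: SD 12.1, one-tailed alpha 0.05 (z = 1.645), power 80% (z = 0.842), attrition 5%.

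n per group = 2 × (1.645 + 0.842)² × 12.1² / d²

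| Difference d (mmHg) | n per group, one-tailed | after 5% attrition | total |
|---|---|---|---|
| 6 | 50.3, rounded up to 51 | 51 / 0.95 = 53.7, so 54 | 108 |
| 4.5 | 90 | 95 | 190 |
| 3 | 202 | 213 | 426 |

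The stated 51 and 108 are reproduced exactly at 6 mmHg, and a t-based calculation gives 50.98. They are not reproduced elsewhere in the 3-6 mmHg range. A two-sided test at 6 mmHg would need 64 per group.

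**2. Power of 51 per group for a difference in means.** Standard error = 12.1 × √(2/51) = 2.396. One-tailed power = Φ(d/2.396 − 1.645).

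- d = 6: Φ(0.859) = 80.5% (70.7% two-sided)
- d = 4.5: Φ(0.233) = 59.2%
- d = 3: Φ(−0.393) = 34.7%

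The smallest difference detectable with 80% one-tailed power is (1.645 + 0.842) × 2.396 = 5.96 mmHg.

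**3. Compare with yes/no forms.** The article gives no event rates for these, so this step is illustrative. Assume normal data, SD 12.1, a true shift of 6 mmHg, and the usual two-proportion formula with pooled variance under the null:

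n = [1.645 × √(2p̄(1−p̄)) + 0.842 × √(p₁(1−p₁) + p₂(1−p₂))]² / (p₂ − p₁)²

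- Responder, drop of at least 3 or at least 6 mmHg, control-arm mean drop 0 or 3: 40% v 60%, 31% v 50% or 50% v 69%, needing 80-82 per group. Power with 51 is 62-63% one-tailed.
- Systolic pressure at or below 130 mmHg, assumed control-arm mean 130 to 150: 81-176 per group. Power with 51 is 38-63% one-tailed.

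Neither form gives 51 per group under these assumptions. The sample size fits a continuous comparison of means.

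**4. Timing.** Study design and hypothesis 1 put T3 at three months post-intervention. Enrolment and randomization puts T2 at 3 months post-baseline, T3 at 6 months and T4 at 9 months post-intervention, which it equates with 12 months post-baseline. Since 3 + 9 = 12, the T4 statement is coherent. For T3, 3 + 3 = 6, so three months post-intervention is six months post-baseline. The 6 in that section agrees with the other sections only if it counts from baseline, but the sentence attaches it to the intervention. A corrected endpoint should give both time origins.

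**The case against.** The strongest reply is that this is one endpoint loosely worded.

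- The Abstract's 3-6 mmHg is the same range as the planning difference in the Power analysis.
- The Patient eligibility sentence goes on to describe instruments, so it is about measuring pressure, not assigning a status.
- Hypothesis 1 fixes a comparison with standard care at T3, and Data analysis compares blood pressure by t-tests.

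All of this stands. A reader might infer three incompatible endpoints from which the most favourable could be reported, but the article does not support that. It defines no binary control outcome, and hypothesis 1 rules out a one-arm before-after test as the primary comparison, so regression to the mean in one arm is not the primary problem. The McNemar and chi-squared tests are for binary variables that are not named.

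A reader might also see conflicting outcome thresholds at 130 mmHg. Those figures are an entry rule, a participant goal and a slip in a feasibility estimate. None is an outcome cut-off.

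Finally, treating 3-6 mmHg as a closed interval for each person gives a striking result. If the SD of change were 12.1, about 9-10% of participants would fall inside it whether the true mean drop were 0, 3, 6 or 9 mmHg. That is a reading the plan does not adopt, and 12.1 is given as an SD of systolic pressure, not of change. Read as at least 3 mmHg, the proportion rises from 40% to 50%, 60% and 69% over the same means.

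The reply does not remove two faults: the Abstract states an effect size as the outcome measure, and the term that names the primary outcome elsewhere is undefined.

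**Conclusion.** The point holds as a defect of definition. The primary outcome is stated wrongly in the Abstract, named by an undefined term in two sections, and left open as to level or change in hypothesis 1. The sizing and the t-tests point to a between-group difference in mean systolic pressure.

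The stated power belongs to that form alone among those checked, and with a limit that the 3-6 mmHg range conceals: about 80% at 6 mmHg one-tailed, and about 35% at 3 mmHg. These figures use only the article's inputs. The comparison with binary endpoints rests on assumed normality, control-arm means or drops, and a 6 mmHg shift. It shows that the choice of form matters, not that the trial is underpowered for an endpoint it has adopted.

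**What to change.** State one primary endpoint in the Abstract, Study aims, Study hypotheses and Patient eligibility sections, for example: the between-group difference in mean systolic blood pressure (mmHg, continuous) at three months post-intervention, that is six months post-baseline. Reconcile the T3 timing in Study design and in Enrolment and randomization at the same time.

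Estimate the difference by ANCOVA with baseline systolic pressure as covariate, in place of an unadjusted t-test. Baseline systolic pressure is already collected and is a stratification factor, so no new data are needed, and the level-or-change question largely falls away because both give the same adjusted treatment difference.

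Remove 3-6 mmHg from the outcome statement, keep the planning effect in the Power analysis, and name 6 mmHg as the value that yields 51 per group.

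Drop control as the name of the primary outcome, or define it as a secondary outcome with one cut-off that places every reading on one side only. Correct the Feasibility sentence, which attaches the word control to pressures above 130 mmHg.

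The cost is minor rewording and a slightly different primary model. The sample size is unchanged if 6 mmHg and the one-tailed test are kept.

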**Discussion:**

The management of complex health problems is an increasing component of health care practice, and requires interventions that improve patient outcomes. We describe the preparatory work and baseline data of a single blind, randomized controlled trial involving consumers requiring cross-specialty care with a follow-up period extending to 12 months post-baseline.

**Trial Registration:**

The trial was registered with the Australian and New Zealand Clinical Trials Register (ACTRN12607000044426).

## Background

### Comorbidity burden

The prevalence of chronic diseases continues to increase, necessitating sustained self-management of medications by consumers in the community and long term monitoring by health professionals. Diabetes and chronic kidney disease are two such rapidly escalating global health problems [1], and diabetes is now the most common cause of chronic kidney disease [2]. Irrespective of the cause of chronic kidney disease, the co-existence of diabetes and chronic kidney disease presents a significant health, social and economic burden and negatively influences health status beyond the sum of the effects of each disease: mortality is higher, quality of life is worse, and the burden on health care services is increased [3].

The complexity of the treatment for co-existing diabetes and chronic kidney disease involves comorbidity management, in particular hypertension, to improve disease control and health outcomes. Accordingly, the consumer is required to consult with numerous health professionals in primary and specialist settings who prescribe multiple medications for consumers to manage their health. Taking medications as prescribed is a principal requirement for well-managed chronic diseases. When multiple treatments are required for different health problems, medication-related concerns such as adherence, drug interactions and side effects, can be perceived as more troublesome to consumers than the treatments themselves [4,5].

Adherence can be defined as the extent to which consumers follow the instructions they are given for prescribed treatments [6]. Approximately 50% of consumers do not take their medications as prescribed. Interventions to assist medication adherence in the presence of co-existing chronic conditions have rarely been examined in past work and this research is of a high priority [7,8]. The management of comorbidities is an increasing feature of health care practice.

While medical interventions are very important to manage and prevent further health problems in people with co-existing diabetes and chronic kidney disease, long-term health outcomes depend on the effectiveness of the choices that consumers make for themselves on a daily basis [9]. The quality of shared decision making between health professionals is critical to this process. Medication mismanagement and safety are a cause of great stress and cost to healthcare providers worldwide [10,11]: 3% of all hospital admissions relate to over-use, under-use and inappropriate use of medications [10]. Poorly controlled diabetes and chronic kidney disease lead to blood vessel injury resulting in heart failure, loss of vision, total kidney failure, and limb loss that disrupt the consumer's ability to engage in independent activities of daily living. This paper outlines the methodology of a clinical trial using the CONSORT Statement [12], which is designed to help consumers with diabetes and chronic kidney disease control their blood pressure and to take their medications as prescribed.

### Conceptual framework

The conceptual framework underpinning this project is the modified Health Belief Model (HBM) [13,14]. The model explains short- and long-term health behaviours by focusing on the attitudes and beliefs of individuals, and their perceived threat and net benefits of taking positive health-related action. The modified HBM is based on the understanding that people will take a recommended health action if they believe the action will avoid a negative health condition and they have the confidence or self-efficacy to undertake the action. The five concepts of the modified HBM include: perceived susceptibility to a particular health problem, the severity of the health problem, the benefits and barriers to taking positive health-related action, and self-efficacy [15]. These concepts account for people's readiness to act. The HBM model encompasses modifying or enabling psychosocial influences that affect a consumer's adherence to recommended health actions.

## Methods

### Overview of the study

This trial was designed to improve medication self-management in consumers with co-existing diabetes and chronic kidney disease by testing a multifactorial, consumer-centred intervention to improve systolic blood pressure control and medication adherence in a randomized controlled trial (RCT). Consumer-centred interactive interventions to aid decision-making are an effective way of helping consumers with diverse backgrounds to understand their chronic diseases and complex medication regimens [16].

### Study design

The study is a single-site, single-blind, longitudinal RCT. Participants have been allocated to one of two groups: the intervention group receives a multifactorial intervention designed to improve blood pressure control and medication adherence, and the control group receives standard care offered by the treating hospital's outpatient clinics and primary care provided by the participants' general practitioner. Data are collected at four time points: enrolment baseline data collection (T1), immediately following delivery of the intervention (T2), three months post-intervention (T3) and 9-months post-intervention (T4).

### Study aims

The primary aim of the study were to evaluate the effectiveness of a multifactorial intervention in terms of improved systolic blood pressure control in participants with co-existing diabetes and chronic kidney disease. Secondary aims were to determine the effectiveness of the intervention on medication adherence, medication self-efficacy and general wellbeing in consumers with co-existing diabetes and chronic kidney disease. The extent of the relationship between pill counts, self-report of medication adherence and self-efficacy, and other clinical and surrogate biochemical markers of disease control will also be evaluated.

### Study hypotheses

1. Compared to participants receiving standard care, participants with diabetes and chronic kidney disease who receive the intervention will show greater reduction in blood pressure at three months post-intervention (T3).

2. Compared to participants receiving standard care, participants with diabetes and chronic kidney disease who receive the intervention will show a greater adherence to their prescribed medication regimen at three months post-intervention (T3).

3. Improved medication adherence will be associated with increased systolic blood pressure control at three months post-intervention (T3).

### The intervention

Information derived from the literature and other components of the study were used to develop a multifactorial intervention, the *Me*dicine *S*elf-*M*anagement *I*ntervention (MESMI) to improve blood pressure control and medication adherence. The MESMI consisted of self-monitoring of blood pressure, an individualised medication review, a twenty-minute Digital Versatile Disc (DVD), and fortnightly follow-up telephone contact for 12 weeks to support blood pressure control and optimal medication self-management. All components of the intervention were delivered by a renal specialist nurse with doctoral qualifications trained in motivational interviewing using a checklist and standing script for fidelity purposes.

### Self-monitoring of blood pressure

The intervention nurse taught participants in the intervention group to take their own blood pressure using the self blood pressure measurement (SBPM) guidelines of O'Brien et al. [17] and a clinically validated A&D Medical Pty. Ltd. digital blood pressure monitor (Model UA-787, Japan). Participants were asked to take their blood pressure seated every morning on their non-dominant arm at around the same time after waking before they had their morning antihypertensive medications. Participants were informed that their blood pressure may be higher at this time as they had not yet had their antihypertensive medications for the day. Participants were provided with a booklet to record their daily blood pressures for approximately three months.

